### **9.3 Level of significance to be used**

The threshold for statistical significance will be  $\alpha=0.05$ .

### **9.4 Criteria for termination of the trial**

The trial will be terminated after enrolment of at least 90 patients in each arm, according to the *a priori* sample size calculation. As described above, the sample size may be re-calculated at the interim analysis, in which case the minimum number of patients per group may be increased accordingly.

The trial will also be continuously monitored for safety by an independent Data Safety and Monitoring Board (DSMB), who may recommend termination of the trial at an earlier point if unexpected concerns over patient safety arise.

### **9.5 Procedure for accounting for missing, unused, and spurious data**

**Primary endpoint.** The primary endpoint of this trial involves collection of four serial (daily) venous blood samples for the measurement of rate of change of Ang-2. Missing data may therefore arise for a number of reasons including: premature discontinuation of study gas (not tolerated, safety issues, caregiver or health provider discretion); mortality event prior to complete collection of samples; or patient dropout. Our primary analysis using a mixed-effects linear model takes into account all available data points, and is able to handle missing data.

**Secondary endpoints.** Mortality at 48 hours is expected to be captured relatively completely, whereas 14-day mortality may be subject to loss to follow-up. Patients with missing data will not be included in computation of mortality, and we will report the number of missing cases. In the event that a significant mortality benefit is observed, we will perform a sensitivity analysis wherein patients with missing data are assigned an outcome of death (iNO group) or alive (placebo group), in order to systematically bias results toward the placebo group. If significant differences remain in this analysis, the result will be considered robust to adjustment for missing data. Our alternative analysis using Kaplan-Meier survival curves will censor patients at the point of last contact, in the case of missing data.

For the time to recovery endpoints, missing data will be handled by censoring patients at the time of the last documented time point. For other continuous variables, missing cases will be excluded from the analysis (two-way repeated-measures ANOVA), or will not affect the analysis (mixed-effects linear model).

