***Serious Adverse Event or Serious Adverse Drug Reaction***

*A serious adverse event (experience) or reaction is any untoward medical occurrence that at any dose:*

- *results in death,*
- *is life-threatening,*
- *requires prolongation of existing hospitalisation, or*
- *results in persistent or significant disability/incapacity*

In this trial of critically ill children hospitalized with severe malaria, mortality is expected to occur in approximately 20% of participants who receive standard medical care[90].

Monitoring serious adverse events during the trial is therefore complicated by the fact that death is part of the natural progression of disease, even under conditions of optimal clinical care (Uganda standard of care). We propose to monitor mortality continuously to detect variations above the baseline expected mortality rate, to allow for early implementation of corrective actions, if required.

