**Secondary outcomes**

*Mortality.* Analysis will follow standard methods in other clinical trials for malaria[64, 81, 82]. Mortality at 48 h and 14 days will be coded as a binary variable. Absolute and relative risk reduction will be reported with binomial 95% confidence intervals. Analysis will be by chi-squared test or Fisher exact test if the expected number of deaths is less than five in one or both treatment groups. In addition, we will present Kaplan-Meier survival curves comparing patients treated with iNO compared to placebo.

Time to death will be analysed using survival analysis (Cox proportional hazard model for difference between treatment arms).

*Time to recovery.* Among survivors (subgroup analysis of randomized participants), recovery times will be analysed by survival analysis (Cox proportional hazard model for difference between treatment arms). Time to sit unsupported, time to coma resolution (in the subset of patients with coma at study admission) and time to discharge will be documented by treating clinicians (blinded to intervention). Time to fever resolution, defined as the time required to achieve a temperature  $<38^{\circ}\text{C}$  and the time to maintenance of temperature  $<38^{\circ}\text{C}$ , will be determined from frequent vital sign monitoring. The time required to achieve a reduction in parasite density of 50%, 90% and to undetectable levels will be determined from daily blood smears. Results will be expressed as the median time to each event, with 95% confidence intervals.

*Additional biomarkers* (continuous variables, multiple measurements longitudinally collected) will be analysed using mixed-effects linear models, with the raw value or log-transformed value of the biomarker level as the dependent variable, as appropriate.

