## **9.2 Number of subjects planned to be enrolled**

We will enrol 180 patients (approximately 90 in each treatment arm).

Based on a recent clinical trial of L-arginine as adjunctive treatment for severe malaria, among patients who subsequently recovered, Ang-2 decreased by 2700pg/mL/day (95%CI 1800-3600pg/mL/day)[33]. We assume that a 50% change in this parameter would represent a clinically significant therapeutic effect. By standard calculations for normally distributed data, 80 patients per group will provide 80% power to detect a difference between two treatment arms of 1350pg/mL/day at  $p=0.05$  (two-sided). This corresponds to a 50% difference in the rate of change of Ang-2 between the arms. To account for possible dropout, loss to follow-up, and/or non-evaluable data of 10% of patients, approximately 90 patients per study arm are required.

However, these calculations do not reflect the analytic plan. Therefore, a simulation study was performed. A number of assumptions needed to be made, such as within patient correlation and Ang-2 variability. Patient Ang-2 data were simulated using a

multivariate normal distribution. A simple autoregressive correlation structure was used with correlations of 0.75, 0.5 and 0.25 for lags 1, 2 and 3 respectively. In previous studies, variability appears proportional to the mean[33]. Simulations were run with three different relationships where the standard deviation was taken to be 40%, 50% and 80% of the Ang-2 mean at each time point. Both groups were assumed to start at Ang-2 levels of 15,000 pg/mL and the average values at each of days 1, 2 and 3 based on the hypothesized slopes of Ang-2. One thousand replications were performed at each standard deviation relationship and treatment effect. The mixed effects models were fit and the likelihood ratio test was used to test the hypothesis of no time by treatment interaction at the 5% level (two tailed). Table 4 shows the results of the power simulations.

Table 4: Power simulations for 90 patients per group

| Standard Deviation
(% of mean) | Slope Difference               |                                        |                                        |
|-------------------------------------------|---------------------------------------|----------------------------------------|----------------------------------------|

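### Excluding children with missing day-14 status from the mortality computation drops mainly children last known alive, so 14-day mortality is probably overstated and unequal loss would create a spurious difference

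*Protocol*

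**What the plan says.** Section 9.1 (Secondary outcomes, Mortality) states: "Mortality at 48 h and 14 days will be coded as a binary variable". Absolute and relative risk reductions with binomial intervals come from that variable, and so does the chi-squared or Fisher test. Kaplan-Meier curves and a Cox model for time to death are planned in addition.

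Section 9.5 expects 48-hour status to be nearly complete, "whereas 14-day mortality may be subject to loss to follow-up". Its rule is: "Patients with missing data will not be included in computation of mortality". The number missing will be reported. Two further steps follow:

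- If a significant mortality benefit is seen, missing iNO children are counted as dead and missing placebo children as alive.
- "Our alternative analysis using Kaplan-Meier survival curves will censor patients at the point of last contact".

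Section 4.5 gives an expected hospital stay of 5 to 7 days and places the first follow-up visit 14 days after admission. Section 5.3(b) allows withdrawal at any time.

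**The concern.** A child who dies in hospital has a known outcome. A child with unknown status at day 14 is one who was alive at last contact, in most cases at discharge. Leaving the unknowns out keeps all the known hospital deaths in the numerator and takes mostly survivors out of the denominator.

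Two things follow. The reported 14-day risk is too high unless the lost children died about as often as those with known status. And if the arms lose children at different rates, equal numbers of deaths yield unequal mortality. The survival analysis that avoids most of this is already in the plan, but section 9.5 ranks it as the alternative, so the exclusion rule supplies the reported effect sizes and p-value.

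**Working it through.** **Inputs from the protocol**

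- Mortality: "mortality is expected to occur in approximately 20% of participants who receive standard medical care" (section 8.1), that is 0.20 × 90 = 18 deaths per arm.
- Arm size and loss: "To account for possible dropout, loss to follow-up, and/or non-evaluable data of 10% of patients, approximately 90 patients per study arm are required" (section 9.2).
- Significance level 0.05 (section 9.3).

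**The plan's own figure.** The protocol gives no sample size or power for mortality. The dropout inflation for the primary endpoint reproduces: 80/0.90 = 88.9, so 89, against about 90 stated.

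**Assumptions, not in the protocol**

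- The 10% is an allowance for the Ang-2 analysis. Using it for missing day-14 vital status is an assumption.
- The split of loss by arm is assumed, so a range is shown.
- No lost child died before day 14. This is relaxed below.

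**Formula.** Risk under the exclusion rule = deaths / (90 − lost).

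**Equal loss of 10% (9 children per arm)**

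- 18/81 = 22.2% instead of 18/90 = 20.0% in both arms; risk ratio 1.00.
- A true 20% v 10% contrast becomes 18/81 = 22.2% v 9/81 = 11.1%. The difference is 11.1 points instead of 10; the risk ratio is unchanged.

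**Unequal loss, 18 deaths in each arm**

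| Loss, arm 1 v arm 2 | Risk, arm 1 v arm 2 | Spurious difference | Risk ratio | Type I error |
|---|---|---|---|---|
| 0% v 0% | 20.0% v 20.0% | 0 | 1.00 | 4.9% |
| 10% v 10% | 22.2% v 22.2% | 0 | 1.00 | 5.4% |
| 0% v 10% | 20.0% v 22.2% | 2.2 points | 1.11 | 6.8% |
| 5% v 15% | 21.1% v 23.5% | 2.5 points | 1.12 | 7.2% |
| 0% v 20% | 20.0% v 25.0% | 5.0 points | 1.25 | 11.8% |
| 0% v 30% | 20.0% v 28.6% | 8.6 points | 1.43 | 24.5% |

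Type I error comes from exact enumeration of two Binomial(90, 0.20) arms. All losses (in whole children) are taken from survivors, and the test is section 9.1's: chi-squared without continuity correction, or Fisher when expected deaths fall below five.

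**Borderline results can move either way** (uncorrected chi-squared)

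- 13/90 v 23/90 gives p = 0.062. Dropping nine survivors from the second arm gives 13/90 v 23/81, p = 0.025.
- 11/90 iNO v 22/90 placebo gives p = 0.034. Dropping nine iNO survivors gives 11/81 v 22/90, p = 0.072.

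**If some lost children died.** With a share q of the 9 lost dying, the true risk is (18 + 9q)/90:

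- q = 0: 20.0%
- q = 5%: 20.5%
- q = 10%: 21.0%
- q = 22.2%: 22.2%, equal to the figure under the exclusion rule

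Above q = 22.2% the rule understates mortality.

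**Kaplan-Meier.** If every death precedes every loss and no lost child died, the day-14 estimate is 18/90 = 20.0% in both arms whatever the loss, and type I error stays at 4.9%.

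**The case against.** The strongest reply is that the effect is small and the plan already has safeguards.

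- **Size.** Equal proportional loss leaves the risk ratio alone. With 90 per arm and 20% mortality, the 95% half-width for the difference is 1.96 × √(2 × 0.2 × 0.8/90) = 11.7 points, so an artefact of 2 to 2.5 points is about a fifth of it. This stands.
- **Cause of unequal loss.** Clinical staff are blinded, the control is room air, study gas lasts at most 72 hours, and eligibility requires willingness and ability to attend follow-up. Nothing in the protocol predicts a 20-point gap in loss between arms. This stands too.
- **Safeguards.** Kaplan-Meier and Cox analyses would appear beside the binary result, and any significant benefit is put to a worst-case test. When the extra loss is in the placebo arm, that test holds surviving false benefits to 2.4% or less in every scenario enumerated. But it runs only after a significant benefit. With extra loss in the iNO arm, an apparent harm or a masked benefit never triggers it. Section 9.1 plans Kaplan-Meier curves but does not say that the risk reductions come from them.

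A reader might infer that the missing can only be children discharged alive, so that mortality is certain to be overstated. The protocol does not support that. Withdrawal before discharge is allowed, and alive at discharge is not alive at day 14. A reader might also infer that the trial's main conclusion is at risk; mortality is a secondary endpoint, and the Ang-2 analysis is unaffected.

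**Conclusion.** The point holds in a limited form. The rule keeps all known hospital deaths and drops mainly children last known alive. It overstates 14-day mortality unless the lost died at about the rate seen in the rest, or higher (about 22% in the example).

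At 10% loss the distortion is about 2 points in the level of risk, and about 2 points in the difference if all the loss falls in one arm, with type I error near 7%. It becomes serious only if loss differs by about 20 points between arms (type I error about 12%). These figures rest on 20% mortality, 90 per arm, assumed loss rates by arm and no deaths among the lost. A change is worth making because it is cheap and because section 9.6 would label a later departure from the protocol's analyses as post hoc.

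**What to change.** - In sections 9.1 and 9.5, make the Kaplan-Meier day-14 risk by arm, censored at last contact with Greenwood intervals, the main 14-day mortality result. Take the absolute and relative risk reduction and their intervals from it.
- Remove the exclusion rule for day 14. Keep the binary analysis for 48-hour mortality.
- Run the missing-data sensitivity analysis in both directions (missing iNO dead with missing placebo alive, and the reverse), whatever the main result.

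The cost is wording and one extra sensitivity run; no new data are needed. There is a small downside: Kaplan-Meier assumes non-informative censoring, so it too is approximate if children censored at discharge differ from those still at risk. The two-way sensitivity analysis shows how much that could matter.

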## **9.6 Procedures for reporting deviations from the original statistical plan**

Deviations from the *a priori* statistical analyses described in the protocol will be described and justified in the final report and will be reported as *post hoc* exploratory analyses.

## **9.7 Selection of subjects to be included in analyses**

All randomized subjects will be included in the primary *intention-to-treat* analysis (change of Ang-2 over time). A secondary *per-protocol* analysis may be performed

including only patients with evaluable data who received the study gas for the proscribed duration (72 hours).

HIV co-infection, co-existent bacteremia and/or meningitis, and blood transfusion may affect Ang-2 levels and may represent effect modifiers of iNO treatment. We expect that randomization and blinding will ensure relatively even distribution of these co-variables between treatment and control groups, although these co-variables may add unexplained variance (random error) in the dependent variable (Ang-2). We will therefore conduct a subgroup analysis of iNO effect among HIV negative patients without bacteremia who do not undergo blood transfusion, to examine the role of iNO in this carefully selected patient population. Additional subgroup analyses will be conducted according to other possibly important co-variables: age < 5 years or ≥5 years; cerebral malaria or other severe malaria syndrome (respiratory distress); HIV seropositivity; and severe anemia.

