#### **4.4 Investigational treatment**

*Product:* Gaseous nitric oxide

*Dose:* 80 ppm

*Dosing schedule:* Continuous

*Route:* Inhalation (non-rebreather HiOx® face mask)

*Treatment period:* Maximum 72 hours (may be discontinued earlier if patient recovers and no longer tolerates face mask)

The iNO will be supplied in cylinders that will be appropriately labelled.

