### ***Quality***

#### ***Intervention***

Administration of study gas will be directly supervised by dedicated trial nurses, who will record the time the patient receives the gas during each shift (8h period) on the CRF. Because patients may not tolerate a mask after partial recovery, the time on the study gas may be less than 72 hours.

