**(b) The type and timing of data to be collected for withdrawn subjects:**

If for any reason a subject does not complete the study, the reason will be entered on the CRF. All subjects are free to withdraw from participation at any time, for any reason, specified or unspecified, and without prejudice. The reason for the early termination will be recorded. The time to resolution of the abnormal result, and any clinical sequelae must also be recorded.

Patients for whom study gas is permanently discontinued will continue to have data collected for primary and secondary trial endpoints, including daily bloodwork. Their results will be included in an intention-to-treat analysis.

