**(c) Whether and how subjects are to be replaced:**

At the midway point of recruitment (90 patients enrolled), an assessment will be made of the number of patients with complete and accurate evaluable data. The current

sample size is estimated for a dropout rate of 10%. If treatment discontinuation and/or withdrawal exceeds 10%, a sample size recalculation will be considered to adjust for greater than expected loss of evaluable patients without compromising study power.

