## **6 TREATMENT OF SUBJECTS**

### **6.1 Description of intervention**

*Product:* Gaseous nitric oxide

*Dose:* 80 ppm

*Dosing schedule:* Continuous

*Route:* Inhalation (non-rebreather HiOx® face mask)

*Treatment period:* Maximum 72 hours (may be discontinued earlier if patient recovers and no longer tolerates face mask)

Gaseous NO (delivered with air and oxygen as carrier) at a concentration of 80 parts per million (ppm) will be administered continuously by inhalation (non-rebreather HiOx®

face mask) for a maximum of 72 hours. Subjects in the control arm will receive room air as a placebo for a maximum of 3 days. The iNO dose of 80 parts per million is US-FDA approved for use in neonates (see *INOMax product monograph*).

To monitor the inspired nitric oxide, nitrogen dioxide (NO2) and oxygen concentrations, a US-FDA approved gas monitor will be used. Should the NO or NO2 concentrations fall outside the targeted range, an operator set alarm will sound. The trial manager or designee (unblinded) will be available on a 24 hour basis to respond to monitor alarms.

Nitric oxide will be delivered as long as possible with the above device, up to a maximum of 72 hours. However, as the subject improves in the course of the disease, recovers consciousness, begins ambulating, and/or no longer tolerates the mask delivery system, the study gas may be discontinued earlier than 72 hours. At this point after significant disease resolution, it is expected that the continued benefit of iNO will be negligible. The trial manager or designee (unblinded) will be responsible for initiating the study gas (iNO or room air placebo), monitoring the inhaled NO, NO2 and O2 levels as well as patient methemoglobin levels, responding to any monitor alarms, initiating corrective actions, and informing the treating physicians, if necessary. We will monitor peripheral oxyhemoglobin saturation, and use the minimum inspired O2 concentration (above 21%) required to maintain a PaO2 ≥ 92%.

As a primary safety measure, every patient will be monitored with a US-FDA approved pulse CO-oximeter for methemoglobin and arterial oxygen saturation. This will assure, metabolically, that too much nitric oxide is not being inhaled and that the inspired oxygen concentration is correct.

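### The per-protocol set demands a full 72 hours of gas although 72 hours is only a maximum, and one committed subgroup is defined by transfusion, which can follow randomisation

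*Protocol*

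**What the plan says.** **Per-protocol set.** Section 9.7 puts all randomised children in the primary intention-to-treat analysis. It adds that a secondary per-protocol analysis may be done, "including only patients with evaluable data who received the study gas for the proscribed duration (72 hours"). Section 9.1 makes that analysis conditional on important protocol deviations.

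**Treatment period.** Section 4.4 gives it as "Maximum 72 hours (may be discontinued earlier if patient recovers and no longer tolerates face mask"), and section 4.5 agrees. Section 6.1 says gas is given for as long as possible, but with improvement, return of consciousness, ambulation or mask intolerance "the study gas may be discontinued earlier than 72 hours". Section 4.9 expects this: "Because patients may not tolerate a mask after partial recovery, the time on the study gas may be less than 72 hours".

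**Subgroup.** Section 9.7 commits to estimating the iNO effect among "HIV negative patients without bacteremia who do not undergo blood transfusion", and expects randomisation and blinding to spread these covariates evenly. Section 6.2 lists transfusion among the supportive treatments given as needed during the trial.

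**Replacement check.** At 90 patients, section 5.3(c) assesses how many have complete and accurate evaluable data, and then says: "If treatment discontinuation and/or withdrawal exceeds 10%, a sample size recalculation will be considered". Section 5.3(b) says: "Patients for whom study gas is permanently discontinued will continue to have data collected for primary and secondary trial endpoints, including daily bloodwork". Those children stay in the intention-to-treat analysis.

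**The concern.** A per-protocol set should remove children whose treatment departed from the protocol. This one can remove children whose treatment followed it. Section 6.1 ties early stopping to clinical improvement, so membership depends on an outcome observed after randomisation. If iNO speeds recovery, fewer iNO children than placebo children remain in the set, and those who remain are not comparable between arms. A per-protocol result that disagreed with the primary analysis could then reflect selection alone.

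The not-transfused subgroup has the same weakness. Transfusion can follow randomisation and may depend on the course of illness, so conditioning on it can undo the balance that section 9.7 relies on. Unlike the per-protocol analysis, this subgroup is a commitment, not an option.

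**Working it through.** **1. The passages side by side.** Take a child who recovers on day 2, no longer tolerates the mask, and has gas stopped. Under sections 4.4, 4.5 and 6.1 this is compliant. Under section 9.1 it is not a deviation. Under section 9.7 the child fails the 72-hour condition and is excluded. A child who dies before 72 hours is excluded too; section 8.1 expects overall mortality of about 20%. The documents do not say what share of children will stop early.

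**2. The plan's own figure.** Section 9.2 allows for 10% loss: 80 / (1 − 0.10) = 88.9, so 89 against about 90 stated. It reproduces, and nothing below changes it. No SD is given for the 80 per group. Back-solving gives 1,350 × √(80/2) / (1.960 + 0.842) ≈ 3,048 pg/mL/day.

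**3. Selection in the protocol's own Ang-2 model.** Inputs from section 9.2: start 15,000 pg/mL; correlations 0.75, 0.5 and 0.25; SD 50% of the mean; daily falls of 2,700 (placebo) and 2,700 × 1.5 = 4,050 (iNO). Each child's slope is the least-squares slope over days 0 to 3. The stopping rules are assumptions; the protocol stops gas on no Ang-2 value.

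*Level rule: still on gas at 72 h if day-2 Ang-2 is 9,600 or more.* Day-2 means are 15,000 − 2 × 2,700 = 9,600 (SD 4,800) for placebo and 15,000 − 2 × 4,050 = 6,900 (SD 3,450) for iNO.
- Placebo kept: 50%. iNO kept: z = (9,600 − 6,900)/3,450 = 0.783, so 22%.
- Mean standardised day-2 value among those kept: 0.798 (placebo) and 1.353 (iNO).
- Day-0 means among those kept: 15,000 + 7,500 × 0.5 × 0.798 = 17,992 and 15,000 + 7,500 × 0.5 × 1.353 = 20,074. The retained iNO children started higher.
- Doing the same for days 1 to 3 gives iNO-minus-placebo differences of +2,082, +525, −1,862 and −4,669 on days 0 to 3.
- Difference in daily fall: (3 × 2,082 + 525 + 1,862 + 3 × 4,669)/10 ≈ 2,260.

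Simulation with values clipped at zero gives about 2,270, against about 1,360 in all children.

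| Assumed rule for remaining on gas to 72 h | Per-protocol difference (pg/mL/day) |
|---|---|
| Day-2 level at least 6,900 | about 1,880 |
| Day-2 level at least 9,600 | about 2,270 |
| Day-2 level at least 12,300 | about 2,680 |
| Day 0 to 2 fall under 4,000 | about 690 |
| Day 0 to 2 fall under 6,000 | about 740 |
| Relative fall under 30% to 50% | about 450 to 690 |

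Every rule keeps fewer iNO than placebo children. With equal slopes in the two arms, the same rules give a difference close to zero.

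**4. A second model, not tied to an Ang-2 cut-off.** Assume the daily fall is normal with SD 3,050 and a true difference of 1,350; a recovery score correlated 0.3 to 0.7 with the fall; and 20% to 80% of placebo children off gas early. The 72-hour contrast becomes about 810 to 1,290, and 29 to 141 of 180 children remain. Early deaths are ignored and would shrink the set further.

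**5. Transfusion.** Assume no iNO effect on Ang-2, SD 3,050, and transfusion correlated 0.3 to 0.5 with a slower fall. If 20% are transfused in one arm and 30% in the other, the not-transfused subgroup shows a false difference of about 120 to 220 pg/mL/day, with sign depending on which arm is transfused more. With equal rates it is about zero. The rates are assumptions; the protocol gives none.

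**The case against.** - **Nothing primary is at stake.** This stands. The primary analysis takes all randomised children, and the per-protocol analysis is optional and conditional. The point concerns how secondary analyses are defined.
- **The set does not remove every recovered child.** A reader might infer that only children who are still ill remain. The documents do not support that. Section 6.1 permits earlier stopping without requiring it, and section 4.4 joins recovery to mask intolerance, so a recovered child who tolerates the mask can complete 72 hours.
- **The direction is not established.** A reader might take the level-rule result (about 2,270 against 1,360) as proof of exaggeration. It rests on a rule found nowhere in the protocol. In the same model, rules based on the size of the fall roughly halve the effect or reduce it further.
- **Only transfusion is at issue in the subgroup.** HIV testing and blood culture are study-entry tests under section 4.9, and some transfusions may precede randomisation. The stated aim is to examine a selected population, not to check the primary result. Even so, the claimed balance is not assured for transfusions given later.
- **Ordinary recovery need not trip the 10% check.** A reader might infer from section 5.3(c) that it would. The check starts from evaluable data, a recalculation is only to be considered, recovery is not named on the section 5.3 discontinuation lists, and section 9.5 does name early gas discontinuation as a possible cause of missing samples. What remains is loose wording that can count a child with all four samples as lost.

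**Conclusion.** Section 9.7 conflicts with sections 4.4, 4.5, 4.9 and 6.1 and should be corrected. As written, the per-protocol set excludes some protocol-compliant children and all deaths before 72 hours. If iNO works, it is likely to do so unequally by arm. The size and direction of the bias are unknown: about 450 to 2,700 pg/mL/day against a true 1,350 under the rules tried, and little or none if iNO has no effect. Those figures rest on assumed stopping rules. They show that the contrast cannot be interpreted reliably; they do not predict a result.

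The not-transfused subgroup is open to a similar, smaller bias if transfusion rates differ by arm. The section 5.3(c) wording is a minor clarification. The primary analysis and the planned sample size stand.

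**What to change.** 1. **Section 9.7, per-protocol set.** Count as per protocol every child who received the allocated gas until 72 hours, death, or a stop the protocol permits. Exclude only true deviations, such as wrong gas, ineligibility or gas never started. This reconciles 9.7 with 4.4, 4.5, 6.1 and 9.1 and leaves the treatment period unchanged.
2. **Case report form.** The stop form in section 4.9 records date, time and reason but refers to the section 5.3 criteria. Make sure its reasons include recovery and mask intolerance. Time on gas per shift is already recorded.
3. **Section 9.7, subgroup.** Define it by baseline variables only: HIV status, entry blood culture, and baseline haemoglobin or transfusion before randomisation. Baseline haemoglobin does not answer whether transfusion itself alters Ang-2. If that question is wanted, keep the not-transfused analysis but label it exploratory and non-randomised.
4. **Section 5.3(c), clarification.** Base the 10% check on missing Ang-2 samples, since children off gas continue daily bloodwork.

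The cost is wording and possibly one added reason on an existing form. No additional samples, visits or patients are needed.
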